### Power Calculation

In this experiment, sample size is predetermined by the number of eligible physicians signed up for the SAR (5576 eligible physicians at the time of randomization). 

**Table 3 table3:** Data collection.

Variable		Definition
**Primary outcome**		
	SAR^a^ access	Whether or not eligible physicians accessed the SAR at least once during the 4-month trial (May to August 2017)
**Secondary outcomes**		
	Number of times SAR accessed	A count of the number of times the physician logged in to the SAR in the 4-month period (May to August 2017) prior to the data cutoff date. Multiple log-ins within a single day will only be counted as 1 log-in.
	Adherence to cancer screening: breast (posttrial)	Proportion of enrolled, eligible patients who are up to date with breast screening at the physician level Numerator: screen-eligible, enrolled patients who had a mammogram in the 24 months before the report cut off date per PEM^b^ physician Denominator: breast screening–eligible, enrolled patients per PEM physician
	Adherence to cancer screening: cervical	Proportion of enrolled, eligible patients who are up to date with cervical screening at the physician level Numerator: screen-eligible, enrolled patients who had a Pap test in the 36 months before the report cutoff date per PEM physician Denominator: Cervical screening–eligible, enrolled patients per PEM physician
	Adherence to cancer screening: colon	Proportion of enrolled, eligible patients who are up to date with colorectal tests intended for screening at the physician level Numerator: screen-eligible, enrolled patients who had either a colonoscopy in the 120 months and/or flexible sigmoidoscopy in the 60 months and/or FOBT^c^ in the 24 months before the report cutoff date per PEM physician Denominator: screen-eligible, enrolled patients per PEM physician
**Process measures**		
	Number of calls to CCO^d^	Number of calls to CCO contact center regarding the SAR (May-August)
	Number of calls to ehealth Ontario	Number of calls to ehealth Ontario contact center regarding a ONEID-related issue (May-August)
	Number of participants opting out	Proportion of participants deciding to opt out of receiving the email during the 4-month trial
	Number of participants with emails that bounced back	Proportion of participants with emails that bounced back (ie, inactive email address)
**Subgroup analyses**		
	History of SAR use	PEM physicians who have never logged in, those who have not logged in for 1 year but did previously, and those with 1 or >1 log-ins in the year prior to the trial
	Baseline cancer screening rate: breast (pretrial)	Proportion of enrolled, eligible patients who are up to date with breast screening at the physician level as of March 31, 2017
	Baseline cancer screening rate: cervical (pretrial)	Proportion of enrolled, eligible patients who are up to date with cervical screening at the physician level as of March 31, 2017
	Baseline cancer screening rate: colon (pretrial)	Proportion of enrolled, eligible patients who are up to date with colorectal tests intended for screening at the physician level as of March 31, 2017
	Sex	Sex of physician
	Years in practice	From the year of graduation
	Practice size	Number of patients enrolled to the physician’s practice
	Size of group	The total number of physicians belonging to the group and practicing within the LHIN^e^ Note: physicians who are part of the physician enrollment model group but practicing in another LHIN will not be included in this count
	Payment model	Identifies the specific type (ie, fee-for-service or capitation)
	Rurality	According to postal code of the PEM physician’s primary practice

^a^SAR: Screening Activity Report.

^b^PEM: physician enrollment model.

^c^FOBT: fecal occult blood test.

^d^CCO: Cancer Care Ontario.

^e^LHIN: Local Health Integration Network.

For testing each experimental factor, a sample size of 5576 physicians achieves 95% power to detect an absolute difference of 4% in SAR use (between those with the factor present versus those with the factor absent) using a 2-sided test at the 5% level of significance assuming a control arm proportion of 0.20 (estimated based on prior CCO data). We would consider small differences in proportions of primary care providers accessing the SAR to be clinically important. For example, if an intervention component resulted in only 4% more primary care providers accessing the SAR (ie, 223 more primary care providers) and if each of those primary care providers identified only a few patients overdue for screening, this would result in cancer screening for an additional 500 to 600 Ontarians.

Screening 500 to 600 more people in over 4 months could be expected to lead to cancer diagnosis and appropriate treatment in less than 1 patient [32]. This positive potential outcome should be placed in context, as screening also has potential harms including false positives and complications at a rate dependent on the nature of the test and the risk of the underlying population. For example, if 1000 people are screened for colon cancer, 1 to 2 people will get extra years of life and 35 people will be falsely diagnosed when taking using fecal occult blood test while 2 people will get extra years of life, 5 people will have cancer prevented and less than 1 person will have complications when using flexible sigmoidoscopy [33]. Patients and family physicians should consider the balance of risks and benefits when considering a given screening test, especially as people age [34]. False positives and overdiagnosis can lead to overtreatment and may have negative psychological impacts on patients [35].

### Embedded Process Evaluation

The process evaluation aims to complement the results of the factorial randomized experiment by exploring how and why the email interventions may (or may not) have resulted in changes in accessing and using the SAR [36]. In semistructured interviews (see Multimedia Appendix 4) with primary care physicians, we will explore how the operationalized BCTs target (or fail to target) determinants of their SAR access (Figure 1).

#### Recruitment

Invitation emails will be sent to primary care physicians participating in the experiment, and a Can $150 (US $121) gift card will be offered as an honorarium. Purposive sampling will be used to ensure both primary care physicians who have not logged in to the SAR and those who have logged at least once are included in the sample. We will use convenience sampling (physicians within study investigators’ professional and personal networks) and snowball sampling (asking participants to forward the recruitment email to potential participants in their own networks of physician colleagues). We will seek recruitment of both SAR users and those who have not used the SAR, with sampling continuing until saturation. To the greatest extent possible within feasibility constraints, we will attempt to recruit physicians exposed to each of the 3 factors during the trial. Interviews and recruitment will continue until no new themes emerge and saturation is apparent regarding the information given for both groups of physicians (those who have and have not accessed the SAR).

#### Data Collection

Telephone-based semistructured interviews will be conducted with eligible primary care physicians who received a rewritten email as part of the trial. It is anticipated that interviews will last about 30 minutes. All interviews will be audio-recorded. If participants are unable to retrieve an email they received, we will send them the email with all operationalized BCTs immediately prior to the interview. The interview guide will be pilot-tested prior to use and refined as needed throughout the interview process (see Multimedia Appendix 4). The guide includes specific questions developed for each physician group (ie, those who accessed the SAR and those who did not access the SAR at least once during the trial). The questions are also tailored to the email they received to inform about the potential mechanisms of action by which the included BCTs produced change or not regarding SAR access and use [21]. The interview will also explore general impressions of the redesigned emails and about the SAR more generally.

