### Study Design

This approach follows the MOST framework to optimize and evaluate multicomponent behavioral interventions [20,25]. Factorial experiments allow for the estimation of main effects of multiple factors in a single experiment by combining experimental conditions [26,27]. Thus, such designs are useful options in health behavior research to efficiently compare more than 1 intervention, particularly, as in our case, when there is no expectation that the factors being tested will substantially interact [28,29]. The trial itself is a 2×2×2 factorial randomized experiment with 8 experimental conditions (Figure 2). 

**Table 1 table1:** Content and hypothesized mechanism of change for each behavior change technique.

Items	Behavior change techniques/factors tested		
	Material incentive (behavior)	Anticipated regret	Problem solving
General description^a^	Explicitly link SAR^b^ use to a monetary bonus^c^ (awarded only if achieving high cancer screening rates)	Induce or raise awareness of expectations of future regret about not logging in to the SAR	Provide strategies that aim to overcome identified barriers to accessing the SAR
Operationalization	Logging into the SAR can help you maximize your screening rates and save time when calculating your preventive care bonus.	How would you feel if a patient had a poor outcome because you missed an abnormal test result?	We know accessing the SAR involves work for you and your staff. Here are 3 tips from other Ontario primary care doctors on how to fit using the SAR into your schedule: Email ONE ID at [contact] to register a delegate with eHealth Ontario so they can check your report Book calendar time right now to check your report Tackle a few patients at a time
Theoretical domains framework-based determinants	Reinforcement, intention	Emotions, beliefs about consequences, intention	Behavioral regulation, environmental context and resources

^a^The descriptions of the behavior change techniques are in line with the Behavior Change Techniques Taxonomy (v1) [22].

^b^SAR: Screening Activity Report.

^c^The financial incentive was already available from the Ministry of Health for achieving screening thresholds; the communication emphasizes how use of the SAR can help in attaining the bonus funds associated with these thresholds.

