### Allocation and Blinding

A deidentified list of eligible participants will be exported from CCO to an independent statistician who will allocate participants to receive 1 of the 8 experimental conditions via simple randomization using computer-generated random numbers.

The different email versions (featuring the different BCTs to be tested) (see Multimedia Appendix 3) will be sent out in 45-minute intervals starting from 9 AM on the 10th day of each month (or if the day falls on the weekend, on the next business day) for 4 months between May and August 2017. The emails could not be sent at the same time since the Cancer Care Ontario’s outgoing mail server could not handle sending out all of the emails at the same time. That is why a delivery schedule made up of 9 intervals (each 45 minutes long) was devised. To address the concern raised regarding sending time, we randomized the order in which the email versions would be sent (ie, 1 version sent per interval) per month. Delivery order will be determined via block randomization. 

**Table 2 table2:** Experimental conditions. + refers to the presence of the factor and – refers to the absence of the factor.

Experimental condition	Factor 1: anticipated regret	Factor 2: material incentive	Factor 3: problem solving
1	–	–	–
2	+	–	–
3	–	+	–
4	–	–	+
5	+	+	–
6	+	–	+
7	–	+	+
8	+	+	+

All randomization procedures will be conducted in SAS version 9.4 (SAS Institute Inc). Treatment allocation will be concealed from the research team and CCO collaborators. It is not possible to blind participants as they must receive the intervention and may notice differences in email content and design; however, they are unlikely to be aware of the different components of the email being tested.

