#### Data Analysis

All audio-recorded interviews will be transcribed. Qualitative data will be analyzed using the framework method which involves the organization and summary of qualitative data by both cases (rows) and themes (columns) [37]. Included BCTs and targeted determinants corresponding to the theoretical domains framework will be applied as deductive codes (beliefs about consequences, emotions, intention, reinforcement, and behavioral regulation). A second level of inductive coding will capture mechanisms of action and will seek to link these mechanisms to specific intervention components (BCTs) whenever possible. Open coding will be applied when emerging themes do not align with theoretical domains framework constructs or when participants highlight the intervention’s failure to activate a potential mechanism of action. All data will be coded by 2 independent analysts using NVivo (QSR International Pty Ltd) (GV and 1 member of the research team). A third analyst will be consulted if discrepancies arise and no consensus can be reached. Once common themes are established across all interviews, the analytical framework will be applied and data will be charted in the framework matrix [37]. We will continue interviews until no new themes emerge and then conduct 3 additional interviews to verify saturation of themes.

Quantitative data from the trial (including exploratory subgroup analyses) and qualitative data from the pretrial focus groups and the posttrial semistructured interviews will be integrated and interpreted by 2 members of the team. In keeping with recommendations for triangulation [38,39], findings regarding barriers and facilitators of logging in and using the SAR and regarding primary and secondary trial outcomes will be summarized in 1 table, known as a convergence coding matrix. Convergence of findings across all data sets will be assessed: full agreement (data convergence), partial agreement (complementarity between data), conflicting findings (discord) or silence (finding identified in only 1 data source and no additional sources) [40]. We will examine points of divergence to better understand the relationship between theory and outcomes, find out how an intervention may work or not in particular conditions, and identify areas of opportunity for future research on how interventions could be improved.

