## Appendix

Multimedia Appendix 1 Current version of the monthly email sent by Cancer Care Ontario.

Multimedia Appendix 2 Rewritten email containing the 3 behavior change techniques.

Multimedia Appendix 3 The 8 email interventions.

Multimedia Appendix 4 Semistructured interview guide.

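### Interviewees who cannot find their email are shown the all-technique version whatever their allocation, so reactions to techniques they were never sent risk being coded as mechanisms of trial exposure

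*Protocol article*

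**What the plan says.** The protocol article describes the trial as follows: "The trial itself is a 2×2×2 factorial randomized experiment with 8 experimental conditions" (Study Design). An independent statistician is to "allocate participants to receive 1 of the 8 experimental conditions via simple randomization using computer-generated random numbers" (Allocation and Blinding). Table 2 lists the conditions, and only condition 8 has all three factors present.

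For the interviews, the Data Collection section of the Embedded Process Evaluation gives this fallback for physicians who cannot find a trial email: "we will send them the email with all operationalized BCTs immediately prior to the interview". Later in the same paragraph it says of the interview guide: "The questions are also tailored to the email they received to inform about the potential mechanisms of action". The Data Analysis section adds a second level of coding for mechanisms of action, which "will seek to link these mechanisms to specific intervention components (BCTs) whenever possible". The interview findings then go into a convergence coding matrix beside the primary and secondary trial outcomes.

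Two other statements bear on the point. Under Recruitment, within feasibility limits, "we will attempt to recruit physicians exposed to each of the 3 factors during the trial". Under Allocation and Blinding, treatment allocation is concealed from the research team and the agency's collaborators. The Results section reports 11 completed interviews, with data cleaning and analysis not yet begun.

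**The concern.** The process evaluation is meant to explain why the emails did or did not lead physicians to open their report. That explanation depends on what each physician was actually sent. Under the fallback, a physician from condition 1, whose email contained none of the three techniques, would read all three messages shortly before being asked how the email acted on them.

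A first reaction to the regret message, given on the day of the interview, is not evidence of how that message worked or failed between May and August 2017. The Data Analysis section describes no flag for interviews held under the fallback and no separate code for reactions to unsent content. Such statements could therefore be coded as mechanisms of a technique the physician did not receive, and then be read as agreeing or disagreeing with that technique's estimated effect.

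**Working it through.** The plan gives no figure for this point, so there is none to reproduce. The check is a count over Table 2.

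**Inputs**
- Eight conditions from three on/off factors (Study Design, Table 2).
- Allocation probability of 1/8 per condition. This is an assumption: simple randomization is stated, but no ratio is given.
- Interviewees who cannot retrieve their email are spread over the conditions as the trial population is. This is also an assumption, because sampling is purposive, convenience and snowball.
- 11 interviews completed (Results). The number m who could not retrieve an email is not reported.

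**Step 1: unsent techniques shown under the fallback**

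| Conditions | Techniques sent | Unsent techniques shown | Share |
|---|---|---|---|
| 8 | 3 | 0 | 1/8 = 12.5% |
| 5, 6, 7 | 2 | 1 | 3/8 = 37.5% |
| 2, 3, 4 | 1 | 2 | 3/8 = 37.5% |
| 1 | 0 | 3 | 1/8 = 12.5% |

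Share shown at least one unsent technique: 1 − 1/8 = 7/8 = 87.5%.

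Mean number of unsent techniques shown: (1×0 + 3×1 + 3×2 + 1×3)/8 = 12/8 = 1.5 of 3.

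Each single technique is absent in 4 of 8 conditions, so for any one technique half of the non-retrievers would be shown a message they were not sent.

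**Step 2: sensitivity to sampling by exposure**

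If only physicians exposed to at least one factor are interviewed, condition 1 drops out, and the share is 6/7 = 85.7%.

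**Step 3: share of all 11 interviews**

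Expected share = (7/8 × m)/11.

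| m | Expected number affected | Share of 11 |
|---|---|---|
| 0 | 0 | 0% |
| 1 | 0.88 | 8% |
| 3 | 2.62 | 24% |
| 6 | 5.25 | 48% |
| 7 | 6.12 | 56% |
| 11 | 9.62 | 87.5% |

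Affected interviews are an expected majority of the 11 only if about 7 or more could not retrieve their email.

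**Step 4: the rules side by side**

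The fallback fixes one email for everyone who needs it. The tailoring rule and the mechanism coding both presuppose the allocated email. The two coincide only for condition 8. If the interviewer knows the allocation, the allocated version could have been sent. If the interviewer does not, the questions cannot be tailored for a non-retriever. The article does not say which of these applies.

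**The case against.** The strongest defence is concealment. Allocation is withheld from the research team, and some interviewees come from the investigators' own networks or by snowballing. The text does not show that an interviewer could look up a physician's condition. If not, the all-technique email is the only version certain to contain everything the physician was sent. This is a plausible reason, although the article does not give it. It stands against any claim that sending the allocated version is free. It does not remove the need to separate the reactions later.

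The fallback can also be read as an exception to a general tailoring rule, and not as a flat contradiction. It would serve the wider aim of hearing physicians' overall views on the redesigned emails. Tailored questions may keep the discussion to techniques actually sent, mechanisms are linked to techniques only where possible, and the interview guide (Multimedia Appendix 4), which is not shown, may distinguish recall from reaction. All of this lowers the risk. It cannot undo having read all three messages immediately beforehand, and the article states no step that keeps the two kinds of statement apart.

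A reader might infer more than the documents support:
- *That most interviewees are affected.* The 7 in 8 applies only to non-retrievers, whose number is unreported and could be zero.
- *That the mechanism findings are misattributed.* The text shows a risk, not an established error. It does not say that interviewees are questioned about techniques they were not sent.
- *That physicians who did not log in are hit hardest.* No retrieval rates by access group are given, and an unopened email may still be in the inbox. For someone who never opened the email, even the allocated version would be new material.

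**Conclusion.** The concern holds as a risk to the attribution of mechanisms in the process evaluation. It comes from a rule the article states, not from detail left to another document. Among interviewees who cannot retrieve their email, an expected 87.5% would be shown at least one technique they were never sent, or 85.7% if all interviewees had at least one factor. Both figures rest on equal allocation and on interviewees who mirror it. As a share of the 11 completed interviews, the effect could be anywhere from 0% to an expected 87.5%, depending on an unreported number.

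The randomized comparison, its primary and secondary outcomes and its power are untouched. The issue is worth correcting because the mechanism findings are set beside those outcomes, and because with 11 interviews each one carries noticeable weight.

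**What to change.** - **Where allocation can be made available at interview:** send the version the physician was allocated (the article lists "Multimedia Appendix 3 The 8 email interventions") and ask the mechanism questions about it first. If views on all components are wanted, show the all-technique email only in a separate, labelled last part.
- **Where allocation is still concealed:** record who was shown the fallback email and link allocation once concealment is lifted. Code reactions to techniques not allocated as hypothetical reactions, and exclude them from the mechanism coding.
- **For the 11 interviews already held:** apply the same flag, later linkage and coding. The emails ended in August 2017 and analysis had not begun at submission, so this could still be done before coding is final.
- **In the report:** state how many interviewees were shown the fallback email.

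The cost is small but not zero: a controlled release or later linkage of interviewees' allocation, and fewer interviews contributing to the mechanism coding of some techniques. With the allocated version sent, the expected share of non-retrievers shown unsent content before the mechanism questions falls from 7/8 to 0. Trial power does not change.

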#### Data Analysis

All audio-recorded interviews will be transcribed. Qualitative data will be analyzed using the framework method which involves the organization and summary of qualitative data by both cases (rows) and themes (columns) [37]. Included BCTs and targeted determinants corresponding to the theoretical domains framework will be applied as deductive codes (beliefs about consequences, emotions, intention, reinforcement, and behavioral regulation). A second level of inductive coding will capture mechanisms of action and will seek to link these mechanisms to specific intervention components (BCTs) whenever possible. Open coding will be applied when emerging themes do not align with theoretical domains framework constructs or when participants highlight the intervention’s failure to activate a potential mechanism of action. All data will be coded by 2 independent analysts using NVivo (QSR International Pty Ltd) (GV and 1 member of the research team). A third analyst will be consulted if discrepancies arise and no consensus can be reached. Once common themes are established across all interviews, the analytical framework will be applied and data will be charted in the framework matrix [37]. We will continue interviews until no new themes emerge and then conduct 3 additional interviews to verify saturation of themes.

Quantitative data from the trial (including exploratory subgroup analyses) and qualitative data from the pretrial focus groups and the posttrial semistructured interviews will be integrated and interpreted by 2 members of the team. In keeping with recommendations for triangulation [38,39], findings regarding barriers and facilitators of logging in and using the SAR and regarding primary and secondary trial outcomes will be summarized in 1 table, known as a convergence coding matrix. Convergence of findings across all data sets will be assessed: full agreement (data convergence), partial agreement (complementarity between data), conflicting findings (discord) or silence (finding identified in only 1 data source and no additional sources) [40]. We will examine points of divergence to better understand the relationship between theory and outcomes, find out how an intervention may work or not in particular conditions, and identify areas of opportunity for future research on how interventions could be improved.

